## Method

### Objectives

The PARTNERS2 cluster RCT tests a collaborative care model for people diagnosed with bipolar, schizophrenia, and other forms of psychosis in addition to modified usual care, in comparison with usual care alone. The trial aims to understand the benefits of refocusing mental healthcare for the target group into primary care through provision of a coaching-based collaborative model to assist individuals with their recovery. The primary hypothesis is intervention arm participants will have improved QOL compared those receiving usual care alone.

The secondary hypotheses are that, in comparison with usual care only participants, intervention arm participants will have improved:

hours per week spent in structured activity;mental health wellbeing;physical healthcare;increased experiences of personal recovery.

An economic evaluation will assess the costs, outcomes, and relative cost-effectiveness of the intervention (see Health economics evaluation section below). The study includes a comprehensive mixed-methods process evaluation to assess fidelity to the model, test the programme theory, and gain a more in-depth understanding of the intervention in practice in relation to implementation barriers and facilitators.

### Patient and public involvement

Several different patient and public involvement approaches are embedded into the trial design. The independent steering group and the DMC have patient and carer members. The study sites all recruited local LEAPs and service user posts were created, coordinated by The McPin Foundation. This means that many aspects of the trial have been shaped by expertise from experience, as follows:

The original research design and research question was co-designed with patients, including a co-applicant.The intervention and guidance manuals have all been developed and reviewed with the three LEAPs. Care partner training was co-designed by the LEAPs. Service user researchers delivered elements of this training.The trial outcome measures were selected through a sub-study, which also developed a core outcome set for bipolar. This involved input from the three LEAPs. Patients and carers were part of the final decisionmaking workshop where trial outcomes were agreed.The LEAPs met every 3 months. They reviewed all recruitment materials and contributed to the development of interview schedules; produced a study specific website with video content to aid participant understanding of what taking part would involve; and were kept up-to-date throughout via meetings and newsletters. Service user researchers have been involved in recruitment of participants and undertaking other study roles alongside traditionally recruited research assistants. The role of the LEAPs and service user researchers in the PARTNERS2 programme is the subject of a separate article.^11^
Dissemination will include input from the LEAPs. A LEAP-led dissemination event and accessible dissemination materials for participants, including a video and infographic, are planned.

### Trial design and setting

This is a cluster randomised controlled superiority trial, with randomisation at GP practice level. All participants continue to receive their usual care. The trial is registered as ISRCTN 95702682. See Table 1 for registration details.

The trial was conducted in GP practice research sites within four English geographical regions: Birmingham and Solihull, Cornwall, Plymouth, and Somerset. This represents a varied cross-section of society, including urbanity/rurality, and different levels of ethnic diversity.

GP practices were assessed for capacity and capability to deliver the trial. This included willingness to physically host the Care Partner, including computer access (key intervention role, see intervention description below), and support data collection requirements.

### Study population and recruitment of participants

The study recruited adults with a diagnosis of schizophrenia, bipolar, or other psychoses who either: are seen in secondary care and considered to of be lower risk/need; or are seen only in primary care (further details in Table 3). Figure 1 provides detail of the recruitment process, outlined below.

**Table 3. table3:** Trial entry criteria for research participants

**Inclusion** **c** **riteria** Registered with a participating GP practice (with at least six individuals coded as having severe mental illness), which refer into recruited community mental health teams, within one of the four region NHS Trusts: Birmingham and Solihull Mental Health Foundation Trust, Livewell South West (Plymouth), Cornwall Partnership NHS Foundation Trust, or Somerset Partnership NHS Foundation Trust. Aged ≥18 years A clinical diagnosis of schizophrenia, bipolar, or other types of psychoses Evidence for care need in relation to this diagnosis in previous 2 years (automatic for those in secondary care; assessed from notes for primary care only). **Exclusion** **c** **riteria** Inability to understand English (or access translation services) Inability to give informed consent Significant need requiring ongoing secondary multi-disciplinary care (such as those meeting criteria for assertive outreach or early intervention functions, and therefore defined as higher, rather than lower, risk or need) Currently receiving home crisis care or care in an inpatient or secure setting Those excluded at the discretion of GPs, if it is felt that inclusion in this trial is not within the best interests of their patient Currently participating in a cognitive behavioural therapy, or a psychosocial or medicinal trial for psychosis or bipolar Individuals with a primary diagnosis of dementia receiving secondary care for dementia Individuals with a primary diagnosis of learning disability receiving care from secondary care for learning disability Individuals with ongoing significant and chaotic substance or alcohol misuse, making engagement with trial and intervention problematic

CRN Clinical Research Network EOI Expression of Interest ASAP As soon as possible

**Figure 1. fig1:**
[figure not shown]
Flowchart detailing recruitment of research participants process. ASAP = as soon as possible. CRN = clinical research network. EOI = expression of interest.

Potential participants seen in secondary care were identified from electronic records. Individuals were checked for eligibility by experienced secondary care clinicians and suitability confirmed by primary care staff. Potential participants seen only in primary care were identified from searches of electronic health records that were then checked for eligibility by primary care or clinical research network staff.

After eligibility checks, information packs were posted to potential participants who were asked to return expressions of interest (or wish to decline). Interested participants were contacted by their preferred method. Arrangements to meet at the practice or home were made. They could give informed consent either at the initial meeting or at a later point; participants could choose to complete baseline measures in multiple meetings.

Non-responders were sent an appointment letter, inviting them to an appointment with a researcher. Where capacity allowed, practice or secondary care staff telephoned the participant to remind them (maximum of three attempts). The appointment allowed researchers to discuss the study face-to-face; if, at the end of the discussion, the potential participant wished to consent to participate in the study this could take place a) in the same meeting, if there was time, or b) at an additional meeting if there was not.

Participants were provided with a £10 high street shopping voucher and thank you card as a gesture of gratitude on completion of each data collection appointment (a total of £20 for baseline and follow-up appointments) and for any qualitative interviews. All recruitment documentation was designed in consultation with LEAPs.

### Randomisation and allocation concealment

Practices were randomised to control and intervention groups on a 1:1 basis, stratified by recruiting region and estimated practice psychosis population (small and large), determined by the number of adults categorised as MH001 according to the Quality and Outcomes Framework register 2017/18 (median 70 patients).^12^ Practices were classified as ‘small’ if the MH001 list was <70 and ‘large’ if ≥70 adults.

The Clinical Trials Units (CTU) conducted the randomisation procedure. Allocation was concealed from participants, researchers, and practices until recruitment was complete within each practice (cluster). Researchers then requested unmasking.

After unmasking of a practice, the practice and its participants were informed of the allocation by letter, or the participant’s preferred method of contact. For logistical reasons, researchers conducting follow-up data collection could not be masked. Those conducting statistical analyses are masked from assignment.

### Intervention

The PARTNERS service places a trained secondary mental healthcare worker in primary care (a ‘Care Partner’). Care Partners work collaboratively with the participant, primary care, secondary care, and other organisations, aiming to improve the participant’s QOL, mental health, and physical health care. Place and method of contact was flexible, with contact once every 2 weeks at the start, stepping down to once every 3 months for some, but stepping up to referral into secondary care if required. The manualised model (manual available from authors on request) of person-centred care aims to improve the emotional, social, and mental and physical health needs of people with severe mental illness (SMI). The Care Partners work with participants to develop a shared understanding and utilise coaching techniques with the intention of encouraging participants to:

Be more confident and proactive about their health through supporting participants to improve their self-management skills.Achieve personal goals related to their health or other aspects of their lives on their recovery journey.

Participants receive the intervention for up to 12 months, including a 2-month transition period back to usual care only. Participants on the secondary care caseload remain so for the duration of the trial. For those receiving the intervention, the intensity of usual care was reduced according to a protocol specific to each trust, to the extent that was possible based on their individual risk, governance, and Care Programme Approach procedures.

Care Partners are mental health workers with a variety of backgrounds, and include occupational therapists, social workers, psychiatric nurses, and support workers. They received 2–3 days initial training in the PARTNERS2 collaborative care model, top-up training throughout the study from PARTNER2 study team members, and supervision from trained supervisors. Supervisors included community mental health team managers, mental health nurses, and psychiatrists who all received training in the PARTNERS2 model. GP co-chief investigator (RB) provided cover for supervision during periods of illness or absence.

### Control group

All participants allocated to the control arm of the trial continue to receive usual care, either within primary care only or also with secondary care. This comparator reflects the unmet treatment need that the intervention aims to resolve. Such care is proactive in secondary care, but with variable practitioners and frequency. Primary care includes an annual review and otherwise tends to be reactive, including mental and physical care as clinically indicated.

### Outcome measures

The trial primary outcome is QOL at the primary endpoint, as measured by the MANSA. This is a self-complete questionnaire comprising both objective and subjective questions across different life domains (work and education, personal finances, leisure activities, social life, living situation, family life, personal safety, and health). Objective items (for example, employment status) are described separately and not aggregated. Satisfaction is rated on a 7-point Likert scale (1 = negative extreme, 7 = positive extreme) and scorings are processed to provide three different types of results: separate domain ratings; an overall MANSA score, assessing QOL (the primary outcome); and a general (single item) QOL rating. Staff undertaking data collection were trained in using the measure. The MANSA was collected at baseline and follow-up.

Secondary outcome measures were assessed at baseline and follow-up (listed in Table 4). Data collection forms are available from the authors on request.

**Table 4. table4:** Schedule of assessment for practices and participants

**Activity**	**Pre-baseline**	**Baseline**	**Pilot phase** **6** months	**Month 10** **±30** **days**
Eligibility check	*x*			
Valid informed consent	*x*	*x*		*x*
**Data to inform if full-scale RCT is feasible**				
Practice recruitment rates	*x*	*x*	*x*	*x*
Practice withdrawal rates			*x*	*x*
Participant eligibility rates	*x*	*x*	*x*	*x*
Patient recruitment rates		*x*	*x*	
Participant withdrawal rates			*x*	*x*
**Outcome measures**				
Quality of life (MANSA)		*x*		*x*
Time use (ONS Time Use Survey)		*x*		*x*
Personal recovery: questionnaire about the process of recovery (QPR-15)		*x*		*x*
General health status and quality adjusted life years: EuroQol (EQ-5D-5L)		*x*		*x*
Mental wellbeing: Warwick–Edinburgh mental wellbeing scale		*x*		*x*
Capability measure and quality adjusted life years: ICEpop capability measure		*x*		*x*
NHS resource use: records audit and economic interview				*x*
Experience of care: brief INSPIRE		*x*		*x*
Healthcare monitoring				*x*
**Safety variables**				
Admissions (psychiatric)				*x*
Crisis care (home treatment)				*x*
**Process evaluation**		*x*		*x*
**Impact of COVID-19**				*x*

MANSA = Manchester short assessment quality of life. ONS = Office of National Statistics. QPR = Questionnaire for Personal Recovery. RCT = radomised controlled trial.

NHS and social care service use for the preceding 3 months prior to baseline and follow-up was assessed to estimate service cost. The period of 3 months was chosen to optimise accuracy of recall and scope of service use. Data includes:

outpatient contacts;inpatient stays;primary care consultations; andother health and social care contacts;

The following secondary outcomes were assessed at 10 months only from primary care and secondary care records:

Healthcare monitoring to assess which of the following have been received by the patient within their GP practice:annual health check;blood pressure, lipids, glucose assessed, and whether treatment was changed; andlifestyle interventions (for example, smoking cessation, alcohol, and dietary guidance)Safety variables:number of crisis care episodes and days under home treatment; andmental health admissions and number of days’ inpatient;

#### COVID-19 sub-study

Participants who experienced COVID-19 restrictions during their involvement in the study in both arms are asked additional questions at follow-up. This capitalises on the opportunity to understand how lockdown has impacted on the participants’ mental health, access to physical health care, and the impact of social distancing on usual activities.

#### Retention

Researcher rapport, flexibility in contact, and thank you vouchers were used to enhance retention. Where participants withdraw from either the intervention or the study, reasons for withdrawal will be captured via quantitative and qualitative data where possible.

### Sample size

The initial sample size for the full trial was based on detecting a mean between-group difference of 0.45 points in the overall MANSA score. Assuming a standard deviation (SD) of 0.90, this is equivalent to detecting half a SD. This standardised effect size corresponds to a medium to large effect size, and in line with the target difference for the DIALOG+ trial.^13^

To detect this target difference, and assuming SD of 0.90, coefficient of variation of cluster size of 0.74 and intra-cluster correlation of 0.05, the recruitment target for the full trial was originally 336 participants across around 56 practice clusters. This assumes an mean average of 6 participants per cluster, 20% drop out at the individual participant level, and 10% drop out at the cluster level.

The trial protocol included an interim blinded review of the assumptions underpinning the original sample size calculation. The pre-specified review was based on data from 39 participants with complete baseline and follow-up primary outcome data, and explored the a priori assumption of a correlation of 0.5 between baseline and follow-up MANSA scores, but which had not been included in the original sample size calculation. From the blinded review, the point estimate of this correlation was 0.69 (80% confidence interval [CI] = 0.56 to 0.79), and, as such, it was deemed appropriate to conservatively allow for a correlation of 0.5 in a revised sample size calculation. Retaining all the other original assumptions of the sample size calculation indicated a recruitment target of 270 participants from around 45 GP practices, to achieve 90% power or 204 participants from around 34 GP practices to achieve 80% power, to detect the pre-specified between-group difference of 0.45 units. In December 2019, both the DMC and TSC approved a revised recruitment target of 270 participants.

In January 2020, the study funder mandated that trial recruitment be terminated at the end of February 2020, in line with the recruitment timescales for the funded programme and based on evidence that recruitment numbers would likely provide approximately 80% power (achieving 270 participants would have required a significant costed extension). Following the funder’s decision, the aim was to recruit 204 participants, from approximately 34 GP practices, to achieve 80% power to detect the pre-specified target difference of 0.45 units, based on the underpinning assumptions of SD of 0.9, mean cluster size of 6 participants, coefficient of variation of 0.74, intra-cluster correlation of 0.05, correlation between baseline and follow-up MANSA scores of 0.5, and allowing for 20% drop out at the individual participant level and 10% drop out at the cluster level following randomisation.

### Serious adverse events

The risk of harm associated with trial procedures and the intervention are considered to be low, and therefore only serious adverse events (SAEs) are being collected. Investigators collate and report all SAEs that meet the following definition:

Any untoward medical occurrence or effect that:

results in death;is life threatening;requires hospitalisation or prolongation of existing hospitalisation;results in persistent or significant disability or incapacity;is a congenital abnormality or birth defect; oris otherwise considered medically significant by the investigator. This will include:crisis care (contact with Home Treatment Team), andself-harm.

Planned hospital admissions or attendances for less than 24 hours are not reported. SAEs are recorded in the source data and on the case report form, and are reported to the trials office within 24 hours of awareness of the event by completing and submitting an SAE form.

### Data management and statistical analysis

Processes to ensure the accuracy of the data are detailed in the trial data management plan. Coding and validation have been agreed between the trial team, statistician, and the trial programmer.

Data from case report forms are entered onto the database by researchers and/or CTU staff in accordance with working instructions, and data queries are managed through the use of data clarification forms. Corrections which are self-evident will be agreed with the Chief Investigator (CI).

Statistical analyses are pre-specified and a detailed statistical analysis plan will be agreed by the DMC and signed off by the independent TSC statistician prior to locking of the database. This plan will be available from the authors on request. Results will be reported in line with relevant Consolidated Standards of Reporting Trials (CONSORT) guidelines.^14–16^ The primary analyses will be undertaken according to a modified intention-to-treat principle, including all participants who are randomised and who provide valid outcome data at baseline and 10-month follow-up. For the primary outcome, multiple imputation will be undertaken in order to present a sensitivity analysis of the full intention-to-treat population.

The primary analysis of the primary outcome will be undertaken blinded to allocated group, and will involve comparison of the change in overall MANSA score between baseline assessment and 10-month follow-up between allocated groups. The comparison will be undertaken using a mixed-effects linear regression model adjusted for baseline MANSA score, as well as the stratification factors (region and practice size), and including a random effect term for GP practice to account for the hierarchical structure of the data induced by the cluster randomisation. Results without adjustment for the stratification variables will also be presented. Model assumptions will be checked and appropriate data transformations sought if required. Continuous secondary outcomes will be analysed similarly. All treatment effect estimates will be presented alongside 95% CIs. Additional secondary analyses of the primary outcome will be considered to explore the effect of intervention fidelity and Care Partner availability on the estimated treatment effect, using Complier Average Causal Effect and per-protocol analyses.

### Health economics evaluation

The economic evaluation will assess the costs, outcomes and relative cost-effectiveness of the intervention from the perspective of health and social care services (costs) and patients (health benefits), over the 10-month time horizon of the trial. The primary measure of benefit will be the quality adjusted life years, derived from the EQ-5D-5L, and published utility values recommended by NICE at the time of analysis.

NHS and social care costs will be calculated using the participant questionnaire data and data from the audit of primary care records. This includes hospital inpatient and outpatient services, community-based mental health and social care services and primary care services. Service use data will be combined with the most recent published national unit costs to estimate health and social care costs. Regression analysis will be used to extrapolate the 3-month participant reported service use data to the 10-month time horizon. This will be combined with the audit data to estimate a total cost for each participant.

The cost and health benefit data will be analysed by treatment allocated and include data for all participants whether or not they completed planned care. Single imputation will be used for missing baseline measures of cost, utility, and clinical indicators,^17^ but not missing demographic data. An indicator for missing demographic data will be used. The final imputation strategy will depend on the pattern of missingness. If the data approximate Missing at Random or Missing Completely at Random, multiple imputation from available data will be used, as recommended by Faria *et al*
*.*
^18^

Regression analysis will estimate net costs and net quality adjusted life years of collaborative care (compared to treatment as usual). Incremental cost-effectiveness ratios will be calculated. Bootstrapping will be used to generate cost-effectiveness acceptability curves, the probability collaborative care is cost-effective, and net benefit statistics.

Sensitivity analysis will explore the impact on the conclusions of alternative health benefit measures, alternative methods of estimating costs, and alternative methods to account for missing data.

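### The costing plan does not name the secondary care records that already supply psychiatric admission and home-treatment days, so these costs would rest largely on a 3-month self-report

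*Protocol article*

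**What the plan says.** The Health economics evaluation section of the protocol article sets the analysis "over the 10-month time horizon of the trial" and names two cost sources: "NHS and social care costs will be calculated using the participant questionnaire data and data from the audit of primary care records". On scope it adds: "This includes hospital inpatient and outpatient services, community-based mental health and social care services and primary care services". For the months that the questionnaire does not reach, "Regression analysis will be used to extrapolate the 3-month participant reported service use data to the 10-month time horizon". The extrapolated figure is then combined with the audit data to give each participant's total. A sensitivity analysis on other ways of estimating costs is promised but not described.

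The Outcome measures section, below Table 4, describes the self-report: "NHS and social care service use for the preceding 3 months prior to baseline and follow-up was assessed to estimate service cost". Its items are "outpatient contacts;inpatient stays;primary care consultations; andother health and social care contacts". The same section then turns to records: "The following secondary outcomes were assessed at 10 months only from primary care and secondary care records". These outcomes include "number of crisis care episodes and days under home treatment", together with mental health admissions and inpatient days.

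Table 4 schedules NHS resource use at month 10 from a records audit and an economic interview. It does not say which records are audited.

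**The concern.** The trial extracts psychiatric bed days and home-treatment days from primary and secondary care records for its safety outcomes. The costing section names the questionnaire and primary care records only. Secondary care records are the natural source for psychiatric admissions and home treatment, and they are not mentioned where costs are built.

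Two features of the trial make this more than a matter of tidiness. First, the Intervention section reduces the intensity of usual care in the intervention arm only, and Care Partner contact starts fortnightly and steps down for some participants. A change in crisis or inpatient use is therefore a plausible route to a cost difference between arms, and it could occur early, outside a window at the end of follow-up. Second, lockdown began in March 2020, partway through delivery and follow-up. For some participants the 3-month window and the months before it would fall under quite different conditions.

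The trial could also report one number of psychiatric bed days as a safety outcome and cost a different, extrapolated number.

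**Working it through.** The article gives no figure for this point, so there is none to reproduce.

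**Inputs from the article.** The horizon is 10 months, with follow-up at month 10 ±30 days (Table 4). The recall window is 3 months. There are 200 participants (Abstract), taken here as about 100 per arm.

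**Assumption.** The article gives no admission rate. The 10-month risk of admission, p, is varied over 2%, 5%, 10% and 20%.

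**Step 1: share of the horizon observed by self-report.**
- At 10 months: 3/10 = 30.0%.
- At 9 months: 3/9 = 33.3%. At 11 months: 3/11 = 27.3%.
- The 3 months before baseline lie outside the horizon and add nothing to this share.

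**Step 2: illustrative precision, constant rate and simple scaling.** Let stays arise at rate λ per month with length D (compound Poisson).
- Full observation: variance = 10·λ·E[D²].
- 3-month total multiplied by 10/3: variance = (10/3)²·3·λ·E[D²] = 33.3·λ·E[D²].
- Variance ratio = 33.3/10 = 3.33; standard error ratio = √3.33 = 1.83.

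The rate and the stay length cancel, so the ratio depends on neither. It does depend on the constant rate, the simple multiplication and accurate recall.

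**Step 3: how few events the window may hold.** With constant risk, the chance of an admission starting in the window is 1 − (1 − p)^0.3. The chance that an arm of 100 shows none is (1 − p)^30.

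| Assumed p over 10 months | Admitted, of 200 | With an admission in the window, of 200 | Chance that an arm of 100 shows none |
|---|---|---|---|
| 2% | 4 | 1.2 | 55% |
| 5% | 10 | 3.1 | 22% |
| 10% | 20 | 6.2 | 4% |
| 20% | 40 | 13.0 | 0.1% |

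Counted as stays, p = 10% means −ln(0.9) × 100 = 10.5 stays per 100 participants over 10 months, of which 0.3 × 10.5 = 3.2 fall in the window.

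**Step 4: when the rate is not constant.** If the rate in the first 7 months is k times that in the last 3, the scaled figure has expectation 10λ against a true 3λ + 7kλ. The ratio 10/(3 + 7k) equals 1 only when k = 1. If k differs between arms, the incremental cost of this item is biased. If it is shared by both arms, the item is still mis-scaled.

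**The case against.** The costing section lists its sources and its service categories but does not assign one to the other. The primary care audit may pick up some admissions, and the safety outcomes themselves come partly from primary care records. Table 4 does not restrict the audit to primary care. An article also condenses a fuller protocol, and the mapping of items to sources may be set there or in a separate economic plan. The article justifies the 3-month window on grounds of recall and scope, and the promised costing sensitivity analysis could use the records.

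Much of this stands, and it rules out several stronger readings that a reader might infer:

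- **That a stay in months 0 to 7 contributes nothing to cost.** This would follow only if the audit captured no admissions, which the article does not say.
- **That home treatment is definitely costed from the questionnaire.** It is named neither among the 3-month items nor in the costing section. Its place under other contacts or community-based mental health services is an inference.
- **That the 1.83 ratio applies to incremental cost, the ICER or the acceptability curve, or that one or two late admissions would drive them.** The ratio is for one item under simple scaling. The plan specifies regression, with predictors not stated, and nothing here measures the effect on totals.
- **That these are the rarest and costliest services.** The article gives neither event rates nor unit costs. It also excludes higher-need patients and those currently in crisis or inpatient care, so rates could be low.
- **That the events are discarded.** They are still reported as safety outcomes.

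The objection does not remove the point. The article states its cost sources and its extrapolation method, so this is a stated choice and not merely missing detail. Regression may smooth the estimate, but it cannot recover stays that were not observed. An unspecified sensitivity analysis leaves the base case as it is.

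**Conclusion.** The point holds in a limited form. The stated base case leaves unnamed a more complete source that the trial already collects, and makes the cost of psychiatric inpatient care depend largely on a short window at the end of follow-up. The dependence is qualified by whatever the primary care audit captures, and for home treatment it is inferred.

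The share observed by self-report follows directly from the article's own periods. The precision figure and the event counts are illustrations that rest on a constant rate, simple scaling and assumed admission risks. Bias is possible as well as noise, because the article itself describes changes in care and circumstances during follow-up; its direction and size cannot be given from the document.

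The advantage of the records rests on one further assumption: that the extraction looks back over the whole follow-up. That is the natural reading, but it is not stated. The records also cover mental health admissions only, so other inpatient care stays with the questionnaire in any case. Since cost-effectiveness is part of the trial's stated aim and the data are already being collected, the change is worth making.

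**What to change.** Before the economic analysis is run, amend the health economics plan as follows:

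1. Confirm that the record extraction for admissions, inpatient days, crisis episodes and home-treatment days covers the whole of follow-up.
2. If it does, cost psychiatric inpatient days and home-treatment days in the base case from those counts.
3. Limit the regression extrapolation to services with no records source, including non-psychiatric admissions.
4. Remove overlapping questionnaire items where they can be separated. The article lists inpatient stays without distinguishing psychiatric from other stays, so state the rule for stays that cannot be classified.
5. Keep the questionnaire-based estimate as a named sensitivity analysis.

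The cost is one change to the economic plan and a small amount of work to reconcile the two sources and avoid double counting. If the extraction covers the whole follow-up, no new data are needed for these items.
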